## Abstract

**Introduction::**

Healthy dietary patterns and physical activity (PA) represent important lifestyle behaviors with considerable potential to influence on age-related metabolic health. Yet, data on the combined effects of these lifestyle behaviors on metabolic health including low-grade systemic inflammation in aging populations remain scarce. Therefore, this protocol describes a randomized controlled trial aiming to examine the impacts of healthy dietary patterns alone or combined with PA on metabolic health in middle-aged and older men and women.

**Material and Methods::**

The ORUDIET study is a 3-arm randomized controlled 16-week trial: Healthy Diet (HD), Healthy diet plus PA (HD-PA), and control (CON). The trial is open label, randomized with allocation concealment, parallel groups with passive controls. Participants without overt disease aged between 55 and 70 years, with BMI below 35, a current intake of a maximum of 1 serving of fruit and vegetable per day, and noncompliance to PA guidelines are eligible for inclusion. Participants in HD are instructed to increase fruit and vegetable intake to 5 servings per day (equivalent to 500 g). Participants in HD-PA receive the same dietary intervention as the HD and are additionally instructed to engage in moderate-to-vigorous physical activities for at least 150 minutes per week. The primary study outcomes are changes in metabolic and inflammatory health biomarkers. Secondary outcomes are changes in body composition and perceived health.

**Ethics and dissemination::**

The study protocol has been approved by the ethical review board in Uppsala, Sweden. The results will be published in peer-reviewed journals and disseminated in national and international conferences.

**Trial registration number::**

NCT04062682 Pre-results

## Introduction

1

Population aging is a worldwide trend and is becoming a growing public health challenge. Indeed, aging is associated among others with a gradual decline in physical function leading to an increase in care-dependent older adults with related increases in health care costs.^[1]^ A slight and chronic elevation in circulating biomarkers of systemic inflammation has typically been reported in older adults.^[2]^ This age-related low-grade systemic inflammation is suggested to precede the onset and development of several chronic diseases, including diabetes and cardiovascular diseases.^[2]^ Together with systemic inflammation, abdominal obesity, hypertension, dyslipidemia and hyperglycemia, collectively defined as the metabolic syndrome (MetS), represent a cluster of strong risk factors for the development of chronic diseases.^[3]^

It is postulated that dietary habits are important lifestyle behaviors with a potential to readily impact on obesity and MetS, factors that have a strong inflammatory pathogenesis contributing to a state of metabolic inflammation (i.e., “metaflammation”).^[2]^ Healthy dietary patterns characterized by high intakes of fruit and vegetable, whole-grain products, low fat dairy, nuts and seeds, and limited intakes of saturated fats, sodium, and red meat have been recommended by global health organizations.^[4]^ Unfortunately, global data show that intakes of healthy food items, with fruit and vegetables in particular, are well below recommended amounts^[5,6]^ and approximately 4 million deaths globally have been attributed to poor dietary habits.^[7]^

Recent observational studies have indicated favorable influences of healthy diets characterized by higher fruit and vegetable intakes on several biomarkers of inflammation, including C-reactive protein (CRP), interleukin-6 (IL-6), IL-10, and tumor necrosis factor-α (TNF-α),^[8–10]^ and components of MetS.^[11–13]^ However, studies based on experimental settings exploring the effects of healthy diets characterized by increased fruit and vegetables on markers of inflammation^[14–16]^ and metabolic risk^[17,18]^ have yielded inconclusive results. For example, although beneficial effects on body composition and insulin levels have been reported in middle-aged overweight and obese individuals,^[17]^ others have failed to show corresponding effects in middle-aged adults with MetS.^[18]^ Furthermore, healthy dietary patterns characterized by increased fruit and vegetable have been linked to reductions in levels of pro-inflammatory biomarkers, including plasma CRP, in some^[15,16]^ but not all studies.^[14]^ Notably, data exploring how the adoption of healthy dietary patterns influences on inflammatory and metabolic biomarkers during the aging process, specifically, are scarce. This paucity of data is unfortunate given the increased prevalence of MetS^[19]^ together with elevations in circulating inflammatory biomarkers with advancing age^[2]^ making the growing population of older adults an important target for preventive health efforts.

Moreover, given the well-established health benefits from adhering to a physically active lifestyle, where an amount of 150 weekly minutes in moderate-to-vigorous PA (MVPA) together with regular engagement in strengthening activities are advocated,^[20]^ lifestyle promotion of healthy aging may not be limited to promotion of healthy diet only, but rather in combination with promotion of increased PA levels. However, surprisingly few randomized controlled trials (RCTs) have previously explored whether a combination of a healthy diet characterized by increased fruit and vegetable intakes together with increased PA levels may elicit greater health benefits compared to changes in diet only.^[21]^

Taken together, new knowledge regarding impact of healthy dietary habits alone or combination with PA on cardiometabolic and inflammatory outcomes is warranted, as it can fuel preventive actions aiming to combat age-related inflammatory and metabolic abnormalities in the growing aging population. Therefore, the ORUDIET study protocol outlines a 3-arm RCT designed to determine the impact of healthy dietary pattern alone or in combination with PA on health outcomes in a population of men and women

## Methods

2

### Study design

2.1

The ORUDIET is a 3-arm RCT (start date: February 2020). The trial is open label, randomized with allocation concealment, parallel groups with passive controls and includes a healthy diet group (HD), a healthy diet plus PA group (HD-PA), and control group (CON). This research protocol was designed without patient involvement. Participants were not invited to comment on the study design. ORUDIET trial is registered at www.clinicaltrials.gov as NCT04062682. A CONSORT flow diagram is shown in Fig. 1.

**Figure 1 F1:**
[figure not shown]
CONSORT flow diagram of the ORUDIET trial.

### Study population and group allocation

2.2

A sample of 300 adults (150 men and 150 women; age 55–70 years) are being recruited through local advertisement and screened for inclusion. On the basis of the screened sample, 60 men and 60 women are anticipated to be randomized into 1 of the 3 groups (20 men and 20 women per group). Randomization will be conducted by an independent statistician using computer-generated random numbers. Stratification by biological sex will be conducted. On the basis of data from previous studies, clinically relevant effects on cardiometabolic outcomes can be detected with 20 participants of the same sex per intervention arm, with a statistical power ≥0.8 and an alpha-level set to *P* < .05.

The inclusion criteria for the study are age between 55 and 70 years, current intake of a maximum of 1 serving of fruit and vegetable per day, and noncompliance to physical activity guidelines (less than 150 weekly minutes of MVPA and less than 2 sessions of strengthening activities). The exclusion criteria are body mass index (BMI) >35, food allergies, movement disability, presence of cardiovascular, metabolic, rheumatologic or psychiatric diseases. Participants will attend a medical screening to confirm eligibility for the study entry. During screening, they will provide information on sociodemographics, medical history, and dietary and physical activity behaviors. Randomization is performed by block-design to ensure equal numbers of participants assigned into the 3 groups stratified by sex.

### Intervention

2.3

Participants in HD and HD-PA groups are instructed to increase fruit and vegetable intake to 5 servings per day (equivalent to 500 g) during 16 weeks. Several menus are composed by a nutritionist to achieve guidelines for healthy dietary habits. Participants attend 2 group-based dietary counselling sessions during the start of the 16-week intervention period. During these sessions, participants are helped to identify potential barriers and facilitators for implementing new dietary habits in order to support adherence during the intervention period. In addition, adherence to the healthy diet is reinforced using a behavioral support package (reading materials on guidelines, recipes, and cooking tips on healthy food choices) provided through a digital platform during the intervention period. Participants in HD are instructed to keep their habitual physical activity level.

Participants in HD-PA receive the same dietary intervention as the HD and are additionally instructed to engage in physical activities corresponding to at least 150 weekly minutes of moderate-vigorous intensity according to current guidelines. For this purpose, participants receive a compendium of physical activities all corresponding to a at least moderate intensity. Together with trained staff from Örebro University, participants are helped to choose appropriate activities to perform during the intervention period. The 2 counselling sessions before the intervention also include identification of potential barriers and facilitators for being physically active. A digital platform with behavioral support on adherence to PA guidelines (reading materials on guidelines, tips on activities, equipment, and safety issues) is provided alongside support for healthy diets. Participants in the control group are instructed to maintain their habitual dietary and physical activity habits.

### Primary and secondary outcomes

2.4

The primary outcomes are the changes in metabolic and inflammatory health biomarkers (see biomarkers description below). Secondary outcomes are changes in body composition parameters and perceived health as outlined below.

### Procedure and data collection

2.5

Recruited participants attend a first visit at the laboratory in order to screen for eligibility criteria. Assessments of physical function and medical screening including measurement of blood pressure are performed and dietary intake including fruit and vegetable intake is determined by a food-frequency-questionnaire (FFQ). Participants are instructed to wear an accelerometer for 1 week to assess habitual PA level. Eligible participants attend a second visit for assessment of body composition and blood sample based biomarkers. Questionnaires on facilitators and barriers for a healthy lifestyle and health-related quality of life are administered.

At the start of the 16-week intervention period, participants randomized to HD and HD-PA attend the counselling sessions held by trained personal in promotion of healthy lifestyles. During these sessions, experiences regarding facilitators and barriers for behavioral change are shared between participants. Information on adherence to HD and HD-PA is self-reported bi-weekly using a digital platform. At the end of the 16-week intervention, measurements of physical function, body composition, dietary intake, PA level, and analysis of blood-based biomarkers are repeated.

### Measures

2.6

#### Assessment of dietary patterns

2.6.1

Dietary data are collected using a validated 84-item food-frequency questionnaire (FFQ).^[22]^ Intake frequency has 9 fixed alternatives (never, occasionally, 1–3 times/month, 1 time/week, 2–3 times/week, 4–6 times/week, 1 time/day, 2–3 times/day, ≥4 times/day).

#### Assessment of PA

2.6.2

Habitual PA will be assessed by the Actigraph GT3x (Actigraph, Pensacola, FL) activity monitor during a week. Count cut-points for sedentary time (<100 counts per min), time in light-intensity PA (LPA) (100–2019 counts per min), and moderate-to-vigorous intensity PA (MVPA) (>2019 counts per min) will be applied as previously described.^[23]^ Adherence to PA guidelines is assessed bi-weekly by self-report.

#### Anthropometrical assessments

2.6.3

Body weight and height will be measured using standardized equipment and procedures. Waist circumference is measured to the nearest 0.1 cm with a steel tape at the midpoint between iliac crest and lower costal margin. A bioelectrical impedance measure is performed using the Tanita MC-780 Multi-Frequency segmental body composition analyzer (Tanita, Amsterdam, The Netherlands) allowing to determine total as well as segmental fat mass and fat-free mass for the trunk, left and right arms, and legs. All anthropometric measurements are performed after an overnight fast and participants are asked to avoid alcohol and not to engage in any strenuous physical activity 24 hours before the measurement.

#### Assessment of blood pressure

2.6.4

Systolic and diastolic blood pressures are measured manually after a 15-minute rest in the supine position using a mercury sphygmomanometer.

#### Assessment of physical function

2.6.5

A squat jump test is performed on a force platform (Kistler 9281 B; Kistler Nordic AB, Sweden), where the participant starts from a static position with knee joints bent at a 90° angle. The hands are kept on the hip during the jump. Participants perform 3 maximal trials separated by 1.5 minutes of rest. The highest recorded maximal ground reaction force from the 3 trials is calculated from the concentric phase of the squat jump. Handgrip strength is assessed by standardized procedures using Jamar handheld dynamometer (Patterson Medical, Warrenville, IL). A 6-minute walk test is performed by walking a corridor of 30 m in length during 6 minutes, and the total distance completed is recorded. A 5 sit-to-stand test is performed where participants are instructed to stand fully upright from a chair and sit down and repeat this sequence 5 times.

#### Blood sampling

2.6.6

Blood samples are obtained after an overnight fast and blood is collected by venipuncture from an antecubital vein, centrifuged at 4000 rpm for 10 minutes and stored in −80°C.

#### Assessment of metabolic health biomarkers

2.6.7

The clinical metabolic markers fasting glucose and insulin, glycated hemoglobin, total cholesterol, high-density lipoprotein cholesterol (HDL-cholesterol), triglycerides, aspartate aminotransferase, and alanine aminotransferase are assessed. Prevalence of metabolic syndrome will be determined according to the criteria set by the International Diabetes Federation: waist circumference above ≥94 cm for men and ≥80 cm for women, along with any of the following; raised triglycerides, ≥1.7 mmol/L or specific treatment for lipid abnormalities; reduced HDL-cholesterol, <1.03 mmol/L or <1.29 mmol/L or specific treatment for lipid abnormalities; raised blood pressure, ≥130 mm Hg systolic or ≥85 mm Hg diastolic or treatment of previously diagnosed hypertension; raised fasting plasma glucose, ≥5.6 mmol/L or previously diagnosed diabetes type II.^[3]^

The inflammatory biomarkers IL-6, IL-10, IL-18, fibrinogen, adiponectin, leptin, 12 are assessed using commercially available ELISA kits (Mercodia, Uppsala, Sweden) and high-sensitivity CRP (hs-CRP) is measured using a fully automated immunoturbidimetric assay (Advia 1800; Chemistry System, Siemens, Germany).

For the analyses of molecular lipids (lipidomics), ultra-high performance liquid chromatography combined with quadrupole-time-of-flight mass spectrometry (UHPLC-QTOFMS) will be utilized as previously described.^[24]^ The method is semiquantitative, based on normalization and quantitation of lipid-class specific compounds. In brief, total lipid extraction from serum samples is performed using a chloroform:methanol mixture after addition of internal standards. External standard is added after the extraction. Lipid extracts are then analyzed on the Q-Tof Premier mass spectrometer: Agilent Technologies (Santa Clara, California) with the Acquity ultra performance liquid chromatography BEH C18: Waters (Milford, Massachusetts) 2.1 × 100 mm column with 1.7 μm particles. The data are collected at a mass range of m/z 300 to 1200 with 0.2 s scan duration in ESI+ mode and are processed using the MZmine 2 software: open source software (available at: http://mine.github.io). Lipids are identified using an internal spectral library or with tandemMS, and data are normalized using the internal standards, representative of each class of lipids present in the samples, as previously described.^[24]^

#### Assessment of facilitators and barriers for change in diet and PA behaviors

2.6.8

Questionnaires on perceived barriers for healthy eating^[25]^ and for being physically active^[26]^ are being used to explore barriers for adopting healthier lifestyles. Moreover, semi-structured interviews will be conducted on a total of 20 men and 20 women. The interviews will be partly based on previously published protocols developed to unveil perceptions about age-related changes in diet and PA behaviors.^[27]^

#### Assessment of health-related quality of life

2.6.9

Self-perceived physical and mental component summary scores will be derived from the 36-Item Short-Form Health Survey (SF-36).

### Data analysis

2.7

Data analysis is performed according to the intention-to-treat principle. Mixed-models analysis of variance including within-subject and between-subject factors and related interaction effects are conducted. Moreover, advanced bioinformatics and multivariate statistical approaches (principal component analysis, multinomial logistic regression, neural networks, Bayesian networks, grade-of-membership analysis) will be applied for the analysis of lipidomic data. Results from questionnaires will be summarized based on quantitative measures of frequencies regarding identification of common perceptions of motives, facilitators, and perceived barriers for change in diet and PA behaviors. Material from interviews will be transcribed and analyzed using qualitative content analysis, with the aim of finding the key themes that can enhance understanding of the conditions for lifestyle change. As the interview protocol will be partly based on a previously published theoretical framework, a framework analysis will also be conducted, which involves coding data according to their importance rather than simply frequency following a systematic 5-step procedure.

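### Counselling in the two intervention arms is group-based, but the stated analysis and power statement name no allowance for counselling-group clustering; a recorded group identifier and a partially nested sensitivity analysis would cover it

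*Protocol article*

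**What the plan says.** **Delivery.** For HD and HD-PA, the Intervention section states: "Participants attend 2 group-based dietary counselling sessions during the start of the 16-week intervention period". The Procedure and data collection section adds: "During these sessions, experiences regarding facilitators and barriers for behavioral change are shared between participants". For HD-PA, the sessions have extra content: "The 2 counselling sessions before the intervention also include identification of potential barriers and facilitators for being physically active".

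**Components not described as group-delivered.** These are the menus, the help from staff in choosing activities, the bi-weekly self-report of adherence, and a support package "provided through a digital platform during the intervention period".

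**Control arm.** "Participants in the control group are instructed to maintain their habitual dietary and physical activity habits". No sessions are described for CON.

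**Sample size.** The Study population and group allocation section expects 120 participants to be randomised, 20 men and 20 women in each of three arms. It claims power of at least 0.8 at an alpha of 0.05 with 20 participants of one sex per arm. Clustering is not mentioned.

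**Analysis.** After naming the intention-to-treat principle, the Data analysis section gives the comparative model in one sentence: "Mixed-models analysis of variance including within-subject and between-subject factors and related interaction effects are conducted".

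The article does not state the number or size of the counselling groups, whether a group mixes arms or sexes, or an ICC.

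**The concern.** Individuals are randomised, but in two of the three arms part of the treatment is given in groups whose members influence one another. That makes the design partially nested: possible clustering in HD and HD-PA, none in CON. The sessions are meant to support adherence, so a good or poor group could move the changes of all its members in the same direction.

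A repeated-measures model with subject-level factors handles the pairing of baseline and week 16. Fitted with nothing more, it treats different participants as independent. If the group ICC is positive, the variance between groups is left out of the standard errors, p-values are too small and intervals too narrow. There is also a practical side: group membership is easy to record when the sessions are held and may not be recoverable at analysis.

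**Working it through.** **1. The plan's own figure.** The figure of 20 per sex per arm cannot be reproduced forwards, because no effect size or SD is given. Solved backwards (two-sided 0.05, power 0.80, independent participants), the detectable standardised difference is d = (1.960 + 0.842) × √(2/n):

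- n = 20 per arm (one sex): d = 2.802 × √0.100 = 0.89 (0.91 with the t distribution)
- n = 40 per arm (both sexes): d = 2.802 × √0.050 = 0.63 (0.63 with the t distribution)

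These differences assume no clustering.

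**2. Inputs for the clustering check.**

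- From the article: 40 per arm, equal allocation, alpha 0.05 (two-sidedness assumed).
- Assumed, because the article does not give them: m = 5, 10 or 20 members of the same arm per counselling group, and ICC = 0.01, 0.05 or 0.10.

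**3. Formulas.**

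- Design effect in a clustered arm: DE = 1 + (m − 1) × ICC
- True/naive standard error against CON (one arm clustered): √((1 + DE)/2)
- True/naive standard error for HD-PA versus HD, if groups are formed within arm: √DE
- Actual two-sided alpha: 2 × (1 − Φ(1.96/ratio))

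**4. Worked example, m = 10 and ICC = 0.05.** DE = 1 + 9 × 0.05 = 1.45.

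- Against CON: ratio √(2.45/2) = 1.107, alpha = 2 × (1 − Φ(1.771)) = 7.7%
- HD-PA versus HD: ratio √1.45 = 1.204, alpha = 2 × (1 − Φ(1.628)) = 10.4%

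**5. Actual alpha over the assumed range.**

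| m | ICC | DE | HD or HD-PA vs CON | HD-PA vs HD, groups within arm |
|---|---|---|---|---|
| 5 | 0.01 | 1.04 | 5.2% | 5.5% |
| 5 | 0.05 | 1.20 | 6.2% | 7.4% |
| 5 | 0.10 | 1.40 | 7.4% | 9.8% |
| 10 | 0.01 | 1.09 | 5.5% | 6.0% |
| 10 | 0.05 | 1.45 | 7.7% | 10.4% |
| 10 | 0.10 | 1.90 | 10.4% | 15.5% |
| 20 | 0.01 | 1.19 | 6.1% | 7.2% |
| 20 | 0.05 | 1.95 | 10.7% | 16.0% |
| 20 | 0.10 | 2.90 | 16.0% | 25.0% |

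With ICC = 0 nothing changes. At ICC 0.01 the excess over 5% is about 2 points at most.

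**6. Power.** At the detectable difference from step 1, a correctly adjusted test with m = 10 and ICC 0.05 has power of about 72% against CON and 64% for HD-PA versus HD, before any loss from having few groups. A simulated group-level analysis of HD-PA versus HD, which includes that loss (40 per arm, d = 0.634, ICC 0.05), has about 68% power with groups of 5 and about 50% with groups of 10.

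**The case against.** The strongest reply is that this is silence rather than error. A journal article condenses the protocol, its one-sentence model does not exclude a random group effect, and random-effect structure commonly sits in an analysis plan. That stands to this extent: the article does not show that clustering will be ignored, only that no allowance is named. It does not dispose of the point, because group membership has to be captured when the sessions are run.

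Several stronger readings are tempting, and the article does not support them:

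- **That the intervals are too narrow.** This needs a positive ICC. Only two early sessions are group-based, and the primary outcomes are blood biomarkers measured over 16 weeks, so an ICC near zero is plausible.
- **That the whole intervention is delivered in groups.** Only the counselling sessions are described that way.
- **That group members share a facilitator and a season.** The article mentions only trained staff and gives no start dates by group. If the same staff run every session, facilitator adds no variance between groups.
- **That HD-PA versus HD is hit hardest.** This requires groups formed within arm. The activity content for HD-PA makes separate groups likely, but the Procedure section describes both arms attending the counselling without saying so. If sessions mixed the arms, a shared group effect would partly cancel in this contrast, and the independent-subjects test could even be conservative.

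The size is also sensitive to how sex is handled. If analyses are by sex and groups mix men and women, the relevant m halves. For groups of 10 at ICC 0.05, alpha for HD-PA versus HD is then about 7.4% (the m = 5 row) rather than 10.4%.

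Finally, with few groups the variance component is hard to estimate: groups of 20 leave 40/20 = 2 per arm. This is a good reason not to insist on the clustered model as the primary analysis.

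**Conclusion.** The concern holds in a conditional form. The article describes a source of dependence in HD and HD-PA that is absent in CON, and neither its model sentence nor its power statement names an allowance for it. If the group ICC is positive and the model is fitted as written, standard errors are understated. Against CON, the true standard error is then about 1.01 to 1.40 times the naive one, and actual alpha is about 5% to 16%, for m from 5 to 20 and ICC from 0.01 to 0.10. For HD-PA versus HD the figures are higher, about 5.5% to 25%, but only with groups formed within arm. Group size and ICC are assumptions throughout, so the article supports no single figure, and with an ICC near zero the effect is negligible.

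This is a cheap improvement, not a demonstrated error in the planned analysis.

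**What to change.** 1. Record the counselling group of every HD and HD-PA participant when the sessions are held.
2. State in the Intervention section how many groups are run and whether they are arm-specific.
3. Add to the Data analysis section a prespecified sensitivity analysis with a partially nested model: a random counselling-group effect on the week-16 response in HD and HD-PA, CON participants as singletons, and Satterthwaite or Kenward-Roger degrees of freedom. Report the estimated ICC for the main biomarkers, and interpret with caution any effect that does not hold under this model.
4. If an arm has only one group, say as a limitation that the group effect cannot be separated from the arm effect.

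The cost is one recorded variable and one extra analysis, with no added participants or procedures. The downside is wider intervals and an imprecise ICC when groups are few. Given the loss of power shown above, the sensitivity role is easier to defend than making this model primary.

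### In its usual form the stated mixed-model ANOVA compares raw change between arms, which is valid but less precise than adjusting the week-16 value for baseline

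*Protocol article*

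**What the plan says.** Section 2.7 (Data analysis) of the protocol article gives the biomarker model in one sentence: "Mixed-models analysis of variance including within-subject and between-subject factors and related interaction effects are conducted". It names no individual factor (not group, time or sex) and no covariate. The sentence before it reads: "Data analysis is performed according to the intention-to-treat principle".

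Section 2.4 defines the endpoint as change: "The primary outcomes are the changes in metabolic and inflammatory health biomarkers". Section 2.5 sets the measurement times. Before the intervention, "Eligible participants attend a second visit for assessment of body composition and blood sample based biomarkers". Afterwards, "At the end of the 16-week intervention, measurements of physical function, body composition, dietary intake, PA level, and analysis of blood-based biomarkers are repeated". There is no biomarker sample in between.

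Section 2.2 gives the allocation: "Randomization is performed by block-design to ensure equal numbers of participants assigned into the 3 groups stratified by sex". The plan is 20 men and 20 women per arm, so 40 per arm and 120 in all. The same section claims power of at least 0.8 at an alpha of 0.05 with 20 participants of one sex per arm.

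**The concern.** With one baseline and one follow-up value, the within-subject factor has two levels. In an ordinary within/between ANOVA, the group-by-time interaction is then algebraically the one-way comparison of change scores across the three arms. A change score subtracts the whole baseline value, as if the slope of week 16 on baseline were 1. When the true slope is smaller, the subtraction adds noise and over-corrects any chance baseline difference between arms. Estimating the slope, as ANCOVA does, avoids both.

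What is at stake is the width of the confidence intervals for the arm contrasts. One of these is healthy diet plus physical activity against healthy diet alone, which the Discussion presents as the question of additive benefit.

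**Working it through.** **Inputs.** From the article: two measurement times (section 2.5), change as outcome (section 2.4), 20 per sex per arm and 40 per arm (section 2.2), alpha 0.05 and power 0.80 (section 2.2). Assumed: two-sided testing, equal SD s at both times, and r between 0.3 and 0.9, because the article gives no correlation.

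**The plan's own figure.** The statement that 20 per sex per arm suffices cannot be reproduced, since no endpoint, effect size or SD is given. Solving backwards with the normal approximation, the detectable difference in SDs of the analysed outcome is (1.960 + 0.842) × √(2/n). This is 0.886 for n = 20 and 0.626 for n = 40.

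**Variances.** Per participant:
- change score: 2s²(1 − r)
- week-16 value adjusted for baseline: s²(1 − r²)
- ratio, adjusted to change: (1 − r²) / [2(1 − r)] = (1 + r)/2
- difference, change minus adjusted: s²(1 − r)², which is zero only at r = 1

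**Numbers.** The N-equivalent saving is 1 − (1 + r)/2 = (1 − r)/2. The power column takes an effect with 80% power under the change analysis and gives its power after adjustment, Φ(2.802/√((1 + r)/2) − 1.960). Detectable differences are for 40 per arm at 80% power, in units of s.

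| r (assumed) | Variance ratio | N-equivalent saving | n per arm matching 40 on change | Power after adjustment | Detectable: change | Detectable: adjusted |
|---|---|---|---|---|---|---|
| 0.3 | 0.65 | 35% | 26 | 93.5% | 0.741 | 0.598 |
| 0.5 | 0.75 | 25% | 30 | 89.9% | 0.626 | 0.543 |
| 0.7 | 0.85 | 15% | 34 | 86.0% | 0.485 | 0.447 |
| 0.8 | 0.90 | 10% | 36 | 84.0% | 0.396 | 0.376 |
| 0.9 | 0.95 | 5% | 38 | 82.0% | 0.280 | 0.273 |

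Example at r = 0.5: 2.802/√0.75 = 3.235; 3.235 − 1.960 = 1.275; Φ(1.275) = 0.899.

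**Sex.** A simulation used three arms, 20 per sex per arm and 3,000 runs per setting, with an assumed sex difference in level of 1 SD.
- Sex difference in level only, r = 0.5: in the change analysis the empirical standard error was 0.2203 with and without sex, and power was 0.795 with and without.
- Added sex difference in change of 0.3 SD (assumed): including sex moved power in the change analysis from 0.775 to 0.783 (r = 0.5), 0.780 to 0.791 (r = 0.7) and 0.754 to 0.783 (r = 0.9).
- Same setting, baseline-adjusted analysis: including sex moved power from 0.844 to 0.887, 0.807 to 0.843 and 0.751 to 0.807.

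In the last setting at r = 0.9, adjustment without sex (0.751) did no better than change without sex (0.754). This is the reason to specify sex together with the baseline covariate.

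**The case against.** The strongest objection is that this is a condensed article and no analysis plan is shown. A sentence that names no factor at all cannot be read as excluding a baseline adjustment. A mixed model with a common baseline mean fits the wording and would recover about the same precision as ANCOVA. A change analysis is also valid, and it matches an outcome defined as change. The first part stands as a limit: the criticism applies to the usual unconstrained form of the model. It does not remove the point, because the article does state a model, and the ordinary reading of it is the less efficient one. The match with the outcome definition is no obstacle either. Once baseline is a covariate, the estimated arm difference is the same whether the response is the week-16 value or the change.

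A reader might infer more, and the article does not support it:

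- *That sex is left out, and that this inflates standard errors for markers such as HDL-cholesterol or leptin.* The sentence speaks of between-subject factors in the plural, and the power statement is per sex, so sex may already be in the model. In a change analysis, a stable sex difference in level cancels within each person, as the simulation shows.
- *That the plan contradicts intention-to-treat by dropping participants without week-16 data.* This would follow from a classical complete-case ANOVA. The term mixed models can equally mean a likelihood-based fit that keeps them, so no contradiction is shown.
- *That the trial has no power to spare.* On the article's own claim, an effect detectable with 20 of one sex per arm would have about 98% power with both sexes pooled: 0.886 × √20 − 1.960 = 2.00, and Φ(2.00) = 0.977. The claim cannot be verified, but it gives no basis for saying there is no margin.

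**Conclusion.** The point holds as a loss of precision. Read in its usual form, the analysis in section 2.7 compares raw change, and baseline adjustment would reduce the variance of each arm contrast to (1 + r)/2 of its value. The gain is equivalent to about 5% of the sample size at r = 0.9 and 35% at r = 0.3. It will differ between biomarkers and be small for those that are very stable over 16 weeks. The size rests on an assumed r, equal variances at the two times and a linear relation between baseline and week 16. The stated test is neither biased nor invalid. Naming sex is good practice because it is the stratum, and it helps within the adjusted model; its absence from the sentence is not shown to be an error. This is a recommended improvement, not a correction without which the trial could not be interpreted.

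**What to change.** In section 2.7, replace the model sentence for the continuous biomarkers with an explicit one. Either of these will do:

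- ANCOVA of the week-16 value on arm, the baseline value of the same biomarker, and sex as a fixed factor; or
- a likelihood-based mixed model for the baseline and week-16 values, with baseline means constrained equal across arms so that all randomised participants contribute, and sex as a fixed factor.

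The outcomes in section 2.4 need not be redefined. Baseline biomarkers and sex are already recorded under sections 2.2 and 2.5, so no visit, sample or participant is added. The cost is a change of analysis wording.
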